## Abstract

**Background::**

Mental disorders impose a substantial burden on individuals and society that cannot be fully captured by diagnostic labels or clinial indicators alone. Accordingly, the need for approaches that comprehensively assess patients’ subjective experiences and daily functioning is growing. Patient-reported outcomes (PROs) enable multidimensional assessment from the patient’s perspective and are increasingly important in mental health research. However, prior studies have frequently assessed these domains in isolation using different instruments and assessment schedules, limiting individual-level integration and cross-study comparability. The focus on single diagnostic groups has further impeded transdiagnostic understanding, and the lack of harmonized data standards has restricted data sharing and reuse. This study protocol describes the establishment of the Transdiagnostic Assessment of Mental Health and Sleep (TAMS) registry, a multidimensional PROs registry designed to enable transdiagnostic comparisons across individuals with mental disorders and physical conditions, as well as healthy participants.

**Methods and Analysis::**

We will conduct a nationwide registry-based cross-sectional study in Japan. Participants will include adults with mental disorders, those with physical conditions, and healthy participants, recruited through an online survey company. After providing electronic consent, all participants will complete an online survey providing information on demographics, diagnoses, and treatment. The registry will also capture information on Quality of Life (QOL) as well as related psychosocial factors, psychiatric symptoms, sleep characteristics, and attitudes toward digital health technology. Data collection is planned for March 2026, with a target enrollment of 3300 participants. Planned analyses will validate patient-reported instruments and characterize how these variables are related to QOL.

**Ethics and Dissemination::**

This study has received ethical approval (ID R07-137) and will be conducted in accordance with national information security guidelines, with voluntary participation, digital informed consent, and findings will be disseminated through peer-reviewed publications and plain-language summaries. The registry will be released as a publicly accessible dataset in accordance with the data-sharing guidelines of the FAIR principles (Findable, Accessible, Interoperable, and Reusable).

**Clinical Trial Registration::**

The study has been registered on https://jrct.mhlw.go.jp/ (registration number: jRCT1030250737; registration link: https://jrct.mhlw.go.jp/latest-detail/jRCT1030250737).

## Main Points

1. This study establishes a multidimensional patient-reported outcomes registry that includes not only individuals with mental disorders and physical conditions but also healthy participants.

2. By moving beyond conventional disorder-specific registries, the registry enables systematic comparison across participants, facilitating transdiagnostic analyses.

3. The registry is designed in compliance with the Findable, Accessible, Interoperable, and Reusable (FAIR) principles, ensuring data findability, accessibility, interoperability, and reusability.

## 1. Introduction

Mental disorders substantially diminish individuals’ quality of life (QOL) and impose high societal costs through losses in educational and employment opportunities, impaired interpersonal relationships, and reduced social participation [1]. The economic impact of mental disorders, including rising health care costs and productivity losses, has also attracted international attention [2], highlighting the need for rigorous evidence on the effectiveness and cost-effectiveness of mental health interventions [2,3]. However, treatment outcomes in mental health care are not adequately captured by symptom reduction alone [4]; comprehensive evaluation requires the explicit incorporation of patients’ subjective experiences, functional changes, and broader psychosocial dimensions [4,5]. Patient-reported outcomes (PROs) address this need by providing a standardized and scalable means of capturing patients’ own perspectives of their symptoms and health-related QOL, which can complement clinician-rated measures [6].

Evidence suggests that integrating PROs into clinical care improves outcomes and supports shared decision-making and quality improvement [7,8,9,10]. Nevertheless, the collection of data on PROs in mental health remains fragmented because of the use of different instruments, inconsistent assessment schedules, and misaligned data standards, resulting in siloed datasets and limited comparability [11]. A health registry directly addresses this fragmentation by providing a structured system for the collection, storage, and dissemination of standardized data from defined populations [12]. As health registries use harmonized instruments and aligned assessment schedules, they enable both individual-level integration and cross-study comparability. However, despite the inception of international initiatives such as Australia’s Mental Health National Outcomes and Casemix Collection and the OECD’s Patient-Reported Indicator Surveys [13,14], dedicated research registries for PROs in mental health remain scarce.

Impairments in functioning and health-related QOL are not confined to specific diagnostic categories within mental disorders but are also observed, to varying degrees, in the general population and among individuals with physical conditions [15,16,17]. Given the frequent comorbidity and temporal dynamics of psychopathological conditions, mental burden is also better conceptualized using continuous dimensions spanning multiple symptom domains than discrete diagnostic categories [18]. Accordingly, transdiagnostic multidimensional frameworks such as the General Psychopathology Factor and Hierarchical Taxonomy of Psychopathology have been proposed [19,20]. However, the data available in most mental health registries limit transdiagnostic analyses and the interpretation of outcome measures, as they focus exclusively on individuals with mental disorders and are organized by diagnosis.

Because transdiagnostic research relies on the linkage, comparison, and reanalysis of data from a variety of studies and populations, a unified framework that explicitly meets these requirements is essential [21]. To enable the linkage, comparison, and reanalysis of PROs data across studies and domains, registries must be designed to support reuse and interoperability as well as adhere to the FAIR principles of Findable, Accessible, Interoperable, and Reusable [22], which extend beyond data availability by emphasizing data structures and metadata that anticipate future reuse and networked integration. Despite the growing number of PROs registries, relatively few explicitly implement the FAIR principles in the design stage or transparently document their level of compliance. The introduction of a transdiagnostic PROs registry guided by these principles could facilitate the integrated assessment of core domains that determine patients’ QOL and functioning within a unified framework.

Any new PROs registry should focus on both patients’ health-related QOL as well as psychosocial factors [23,24,25,26]. In addition, it would be important to account for patients’ psychiatric symptoms, sleep characteristics, and attitudes toward digital health technology. First, sleep disturbance is prevalent across a wide range of mental disorders, including depression, anxiety disorders, and developmental disabilities, as well as in physical illnesses such as diabetes, which exemplifies a condition at the intersection of psychiatric symptoms and QOL impairment [27,28,29,30]. Second, recent advances in digital technologies have accelerated the adoption of remote psychotherapy and artificial intelligence (AI)-based support tools for addressing mental health concerns [31,32]; however, their effectiveness and real-world implementation are strongly influenced by psychosocial factors, including users’ and professionals’ attitudes, ethical concerns, and risk perceptions [31,33]. Importantly, sleep characteristics and attitudes toward digital health technology are not independent domains: sleep is a major target of digital monitoring and intervention, and the uptake and sustained use of these technologies depend on users’ digital literacy, trust, and attitudes. Assessing these domains concurrently within a harmonized registry therefore enables participant-level cross-domain analyses that capture the interface between psychopathology and digital health—analyses that are not easily reconstructed from separate studies.

Despite the relevance of these domains, prior studies have largely relied on domain-specific assessment approaches, constraining the reconstruction of multidimensional, patient-level profiles and the examination of cross-domain patterns spanning psychiatric symptoms, sleep characteristics, and attitudes toward digital health technology. Further, studies that have simultaneously collected these domains within a single, harmonized PROs registry using standardized measurement schedules and data structures remain scarce. This study bridges an important gap in research on this topic because it aims to establish the Transdiagnostic Assessment of Mental Health and Sleep (TAMS) registry in Japan. The TAMS registry intends to provide a standardized infrastructure for the multidimensional collection and unified assessment of QOL, related psychosocial factors, psychiatric symptoms, sleep characteristics, and attitudes toward digital health technology. In this study, a transdiagnostic perspective is adopted as a design requirement for the registry, rather than as a theoretical hypothesis to be tested.

## 2. Materials and Methods

### 2.1 Design

The TAMS registry will systematically collect multidimensional data from individuals with mental disorders and physical conditions, as well as from healthy participants in Japan. This proposed framework is expected to support both the psychometric validation of key measures and the exploratory and confirmatory factor analyses (exploratory factor analysis [EFA] and confirmatory factor analysis [CFA], respectively) of the relationships among the clinical, psychosocial, and attitudinal domains. Fig. 1 depicts the registry-level objective, conceptual design, and common data structure of the TAMS registry; it does not intend to represent a fixed temporal or analytic sequence.

**Fig. 1. F001:**
[figure not shown]
**Study overview: TAMS registry framework**. TAMS, Transdiagnostic Assessment of Mental Health and Sleep registry; FAIR, Findable, Accessible, Interoperable, and Reusable.

Reporting will adhere to the Strengthening the Reporting of Observational Studies in Epidemiology (STROBE) guidelines for observational research [34]. Registry planning and governance will be based on the Agency for Healthcare Research and Quality guidelines [35], Checklist for Reporting Results of Internet E-Surveys (CHERRIES) [36], and Standardized Protocol Items Recommendations for Observational Studies (SPIROS 2025) checklist [37]. In addition, the open-science practices of the registry will conform to the FAIR principles [21] (see **Supplementary Materials**).

### 2.2 Participants

Participants will be recruited in March 2026 from a nationwide web-based research panel managed by Macromill, Inc. (Tokyo, Japan). Recruitment will be conducted through direct invitations and study announcements posted on the Macromill website. The Macromill panel has been used in several previous studies [38,39]. Participants will be recruited using prespecified eligibility criteria and stratified quotas by diagnostic category. The provider maintains both general-population and disease-specific subpanels, including pre-identified panelists who have received physician diagnoses of the target disorders at medical institutions. Diagnostic classification will be based on the participant-reported history of physician diagnosis recorded in Macromill’s disease-specific panels, in which disease information is updated annually. By way of confirmation, invitees will additionally complete a screening item upon starting the survey to confirm their current diagnosis; diagnoses will not be independently verified through medical records or structured diagnostic interviews. Only respondents who pass their confirmation stage will proceed to the survey.

Inclusion criteria will be as follows: (1) understanding the study purpose and providing informed consent; (2) registration in a pre-identified disease-specific panel comprising individuals who have received a physician diagnosis of a target disorder and a positive response to an upfront screening item confirming a current diagnosis of one of the following conditions: major depressive disorder, social anxiety disorder, panic disorder, post-traumatic stress disorder, obsessive/compulsive disorder, insomnia, attention-deficit/hyperactivity disorder, autism spectrum disorder, type 1 diabetes, and type 2 diabetes; or registration as a healthy individual based on self-report indicating no current physician-diagnosed disease; (3) age ≥18 years; and (4) ability to respond in Japanese. Exclusion criteria will include the inability to provide informed consent or complete the survey.

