**Aim 1. Psychosocial correlations and measurement foundations for QOL and psychiatric symptoms**					
1a. DQ5-J validation	Patients with mental disorders	Examine the reliability and validity of the DQ5-J.	Target instrument: DQ5-J Validation measures: PHQ-9, GAD-7, EQ-5D-5L	Structural validity: CFA first, EFA only if needed Reliability: Internal consistency (*α*, *ω*), Test–retest (intraclass correlation coefficient) Construct validity: Convergent/discriminant/known-groups validity testing Criterion validity: receiver operating characteristic/area under the curve analysis	Confirmatory
1b. Parental burnout in relation to socioeconomic status, mental health, and sleep	Patients with mental disorders	Examine the associations of BPBs with current SES, psychiatric symptoms, neurodevelopmental traits, sleep measures, and QOL.	Exposure: BPBs Correlates/outcomes: current SES, psychiatric symptoms (e.g., PHQ-9, GAD-7, K6), neurodevelopmental traits (e.g., AQ-28, ASRS), sleep measures (e.g., ISI, RU-SATED), and QOL (e.g., SWLS and EQ-5D-5L)	Pearson/Spearman correlations Partial correlations adjusting for age, sex, and prespecified demographics FDR correction (Benjamini–Hochberg procedure, *q* < 0.05) Outlier identification and sensitivity analyses	Confirmatory
1c. Shift-and-persist coping strategies in relation to mental disorders	Patients with mental disorders, healthy participants	Examine whether individual differences in SAP coping strategies are associated with case–control status across multiple mental disorders and whether higher SAP are associated with a lower likelihood of belonging to patient groups than a shared non-clinical control group.	Exposure: Shift-and-persist coping strategies (quartiles; continuous in sensitivity analyses) Outcomes: case–control status within each mental disorder panel (patient vs non-clinical control) Covariates: age, sex, education, SES (childhood and current)	Chi-square tests, logistic regression (odds ratios, 95% confidence intervals), Cochran–Armitage trend tests, Firth-penalized logistic regression, FDR correction (Benjamini–Hochberg procedure, *q *< 0.05), sensitivity analyses	Confirmatory

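### Sub-study 1c bars physical illness in controls but not in cases, and its listed covariates have no term for it, so its odds ratios may not be specific to mental disorder

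*Protocol article*

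**What the plan says.** Section 2.2 of the protocol article sets different entry rules for the two sides of the comparison.

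- **Controls** enter by "registration as a healthy individual based on self-report indicating no current physician-diagnosed disease". This covers physical as well as mental disease.
- **Cases** need panel registration and "a positive response to an upfront screening item confirming a current diagnosis of one of the following conditions". Nothing is said about other illness.
- **Exclusions** apply to everyone and do not touch comorbidity: "Exclusion criteria will include the inability to provide informed consent or complete the survey".

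Table 1 labels Sub-study 1c confirmatory. Its population is "Patients with mental disorders, healthy participants", so the two diabetes groups are not in it. The hypothesis is that higher SAP goes with a "lower likelihood of belonging to patient groups than a shared non-clinical control group", and the outcome is defined separately for each disorder panel. The adjustment set is "Covariates: age, sex, education, SES (childhood and current". The analyses include logistic regression, Firth-penalised logistic regression, Benjamini–Hochberg correction and sensitivity analyses that the row does not describe.

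Table 1 names the diabetes groups only in Sub-study 2b, although the Discussion gives direct comparison of mental, physical and healthy groups as a purpose of the registry. The limitations cover panel selection, diagnostic misclassification, the cross-sectional design and careless responding. They do not mention the difference in entry rules.

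**The concern.** Physical illness is 0% among controls by rule and uncontrolled among cases. Any SAP difference that goes with physical illness therefore enters the comparison as if it belonged to the mental disorder.

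The same entry rule applies to every comparison. If the relation between SAP and physical illness has the same sign across panels, all the odds ratios move the same way. The result could look like a consistent association across disorders, which is the pattern that 1c sets out to find. False discovery rate correction deals with the number of tests and does nothing about a bias that they share.

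The cause is the entry rule and not the sharing of controls. Separate control groups recruited under the same rule would carry the same bias.

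**Working it through.** **1. The plan's own figures.** Section 2.6 gives 200–300 per group and a detectable d of 0.28 to 0.23. With two-sided 5% and 80% power (assumed, since neither is stated), d = (1.96 + 0.84) × √(2/n). This gives 0.280 at n = 200 and 0.229 at n = 300, so the plan's figures reproduce. The plan gives no figure for the 1c odds ratios.

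**2. Number of comparisons.** Section 2.2 lists ten conditions. Taking out type 1 and type 2 diabetes leaves eight panels, if insomnia and the developmental conditions count as mental disorders.

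**3. Size of the bias, illustrated.** The document gives neither the share of cases with physical illness (q) nor the SAP difference that goes with it (e, in SD). Both are assumptions here. With no mental-disorder effect:

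- gap between cases and controls = q × e
- odds ratio per SD of SAP = exp(−gap)
- odds ratio for top versus bottom quartile = exp(−2.54 × gap), where 2.54 SD is the distance between the two quartile means of a normal variable
- z at 250 per group = gap / √(2/250)

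| e (SD) | q | gap (SD) | OR per SD | OR, extreme quartiles | z | chance of p < 0.05 |
|---|---|---|---|---|---|---|
| 0 | any | 0 | 1.00 | 1.00 | 0 | 0.05 |
| 0.2 | 30% | 0.06 | 0.94 | 0.86 | 0.67 | 0.10 |
| 0.3 | 40% | 0.12 | 0.89 | 0.74 | 1.34 | 0.27 |
| 0.4 | 50% | 0.20 | 0.82 | 0.60 | 2.24 | 0.61 |

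The last column is for an unadjusted comparison of means before false discovery rate correction. It is an indication, not the error rate of the planned analysis. If physical illness went with higher SAP, the odds ratios would lie above 1 instead.

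**4. A second model gives a similar picture.** Split SAP into low and high. Let ORp be the odds ratio between low SAP and physical illness. Then p = (1 − q) × 0.5 + q × ORp/(1 + ORp), and the spurious odds ratio for low SAP is p/(1 − p). For q = 0.4 and ORp = 2: p = 0.300 + 0.267 = 0.567, giving 1.31. Over q = 0.1–0.5 and ORp = 1.2–3.0 it runs from 1.02 to 1.67.

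**5. Does adjustment or restriction remove it?** I simulated the middle row of the table with 250 per group, no mental-disorder effect and 1,500 runs, using Firth logistic regression:

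- as listed, without an illness term: OR per SD 0.886
- with a physical-illness term: 0.999
- cases without physical illness only: 0.999

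The last two agree because every physically ill person in the comparison is a case. That stratum says nothing about SAP, so the coefficient comes from the illness-free people. The Firth penalty keeps the illness coefficient finite.

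**6. What would the diabetes groups do as controls?** All of them are physically ill, against 40% of cases in the illustration. If diabetes lowers SAP like other illness, the gap is 0.3 × (1 − 0.4) = 0.18 SD in the opposite direction, against 0.12 SD with healthy controls. The expected OR is exp(0.18) = 1.20, and the simulation gave 1.19.

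**7. Precision of the extra analyses.** Removing 20–40% of cases raises the detectable d to 0.30–0.32 at 200 per group and 0.24–0.26 at 300. One panel against both diabetes groups pooled (200 v 400, or 300 v 600) gives 0.24 or 0.20, before anyone with a mental disorder is removed.

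**The case against.** The strongest defence is that 1c already words its hypothesis as patient groups against non-clinical controls. For that contrast the odds ratios are valid. Healthy controls are a common choice, and the Discussion disclaims prespecified causal inference. This stands as far as it goes: the problem is one of interpretation, arising when the result is read as being about mental disorder, as the sub-study's title and objective invite.

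A second defence is that Table 1 is a summary and that the sensitivity analyses for 1c are specified in supplementary materials not shown here. They may already deal with the point, so I put little weight on the absence of a sensitivity analysis. The entry rule, the population and the covariate list are stated in the article itself.

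Third, the size is wholly assumed. This also stands, and zero belongs in the range.

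Three stronger readings are tempting but not supported:

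- **That adjustment cannot help because no control is ill.** Step 5 shows that it can, with a method the plan already lists.
- **That the diabetes groups would separate mental from physical illness.** They reverse the imbalance. They represent one kind of illness, and section 2.2 does not require them to be free of mental disorder.
- **That the remedy certainly needs no new data.** The abstract says "all participants will complete an online survey providing information on demographics, diagnoses, and treatment", but section 2.4 lists no physical-comorbidity item. Whether comorbidity is recorded is an inference.

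**Conclusion.** The concern holds as a matter of specificity. Cases and controls in a confirmatory sub-study differ by rule in physical illness, the listed covariates do not account for it, and the limitations do not mention it. If SAP is related to physical illness, all eight odds ratios are biased, in the same direction provided the relation has the same sign across panels.

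The size cannot be taken from the document. Under assumed inputs it runs from nothing to an odds ratio of about 0.82 per SD, with 0.89 for 0.3 SD and 40% of cases ill. A reader might infer that the 1c odds ratios are invalid or that the design cannot be rescued. The documents support neither: the odds ratios describe patients against disease-free people, and one restricted or adjusted analysis removes the imbalance if comorbidity is recorded.

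**What to change.** In Table 1, row 1c:

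(a) If the diagnoses collected in the survey include physical comorbidity, add a sensitivity analysis restricted to cases without physical disease. Equivalently, add a physical-illness term to the Firth model already listed.

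(b) As a secondary, bracketing comparison, fit the same models against the diabetes groups, leaving out those with a reported mental disorder where this is recorded. State that all of these controls are physically ill, so the bias runs in the opposite direction. The comparison is therefore conservative and not a clean separation, and failure to hold there does not by itself refute an association.

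(c) Unless the association survives (a), or holds in (b) where (a) is not possible, report it as patients versus disease-free people and not as specific to mental disorder. List the asymmetry in entry rules as a limitation.

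The cost is table and analysis wording, with no extra recruitment. Part (a) depends on comorbidity having been recorded. The restricted analysis will have wider intervals, and the claim may end up weaker.
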